### Well-nourished controls

Controls are children drawn from the same hospitals and communities as cases with SAM (including well-nourished sibling controls), who are aged 6–59 months (matched to enteropathy substudy children within age bands), well-nourished (WHZ >–1) and clinically well (no acute illness or current infections) with known HIV status. Controls are categorised into two groups: well-nourished HIV-positive (group B) and well-nourished HIV-negative (group D), as shown in table 1. Children with underlying chronic gastrointestinal disease or a known malignancy are ineligible. Well-nourished controls provide comparison biomarker data for all the laboratory substudies.

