**Ethics and dissemination:**

The study is approved by the local and international institutional review boards in the participating countries (the Joint Research Ethics Committee of the University of Zimbabwe, Medical Research Council of Zimbabwe and University of Zambia Biomedical Research Ethics Committee) and the study sponsor (Queen Mary University of London). Caregivers provide written informed consent for each participant. Findings will be disseminated through peer-reviewed journals, conference presentations and to caregivers at face-to-face meetings.

Strengths and limitations of this studyRigorous collection of longitudinal data on morbidity, mortality and nutritional status during inpatient care and for 48 weeks after initial admission for severe acute malnutrition (SAM) in HIV-positive and HIV-negative children.Laboratory substudies investigating enteropathy, microbiota, metabolomics and immune cell function provide a unique opportunity to understand which pathogenic pathways contribute to SAM and whether these processes normalise with nutritional rehabilitation.High loss to follow-up due to participants returning to home settings following hospital discharge.The clinical heterogeneity of the study participants, including comorbidities such as infections, may make it challenging to identify the specific causes of clinical outcomes.Potential bias in recruiting well-nourished controls only from hospitals will be reduced by inclusion of community-based controls, including well-nourished siblings of children with SAM.

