## Study design

HOPE-SAM is a longitudinal observational cohort study, enrolling between 600–800 children aged 0–59 months admitted with complicated SAM to the tertiary paediatric wards at two sites in Zimbabwe (Parirenyatwa Hospital and Harare Children’s Hospital) and one in Zambia (University Teaching Hospital, Lusaka). Both HIV-positive and HIV-negative children will be enrolled. Throughout this paper, ‘SAM’ refers to all children, regardless of HIV status; where analyses specifically compare children by HIV status, groups are identified as HIV-positive children with SAM (HIV-SAM) and HIV-negative children with SAM. All participants with SAM are followed for 48 weeks post discharge, with longitudinal data collection and blood sampling. The study contains four nested substudies as shown in figure 1. A subgroup of children will be recruited to the enteropathy substudy for which they will have the same follow-up procedures but more intensive biological specimen collection including stool (all time points), urine after lactulose-mannitol (LM) challenge as an assessment of intestinal permeability and nasogastric aspirate (baseline only); these children are also included in microbiota and metabolomics substudies. Children with SAM for whom blood samples are available are included in the immunology substudy, for which circulating inflammatory mediators will be assayed; functional cellular immunology assays will be conducted for all children in the immunology substudy with sufficient sample volume (>2 mL) recruited after June 2017. A group of healthy children recruited from the same hospitals and communities, who are well-nourished and matched to children in the enteropathy substudy by age and HIV status, will have data and specimens collected to provide normative data for the laboratory substudies; these well-nourished controls will not be followed longitudinally.

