### Eligibility for enteropathy substudy

Children with SAM aged 6–59 months with a nasogastric tube in place (or due to be placed) are categorised into four groups (HIV-positive oedematous (group A -I); HIV-positive non-oedematous (group A-II); HIV-negative oedematous (group C-I) and HIV-negative non-oedematous (group C-II)) as shown in table 1. Children meeting eligibility criteria will be enrolled throughout the study recruitment period until sufficient specimens have been collected from the groups shown in table 1. Children in the enteropathy substudy are stratified into age bands (6–11 months, 12–23 months and 24–59 months) to enable age-matching of well-nourished controls. Children with underlying chronic gastrointestinal disease or a known malignancy are ineligible.

**Table 1 T1:** Enteropathy substudy groups

Children aged 6–59 months	SAM*		Well-nourished controls WHZ>–1
	Oedematous†	Non-oedematous	
HIV-positive (HIV PCR+ if <18 months; HIV antibody+ if >18 months)	n=50 (group A-I)	n=50 (group A-II)	n=100 (group B)
HIV-negative (HIV PCR– if<18 months; HIV antibody – if>18 months)	n=50 (group C-I)	n=50 (group C-II)	n=100 (group D)

Note that children below 6 months of age are excluded from the enteropathy substudy to avoid interrupting exclusive breast feeding during the lactulose-mannitol test.

*SAM defined according to WHO criteria.

†Presence of bilateral pitting pedal oedema.

SAM, severe acute malnutrition; WHZ, weight-for-height Z-score.

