### Enteropathy substudy

The sample size was estimated using previously reported values for LM ratios, which remain a widely used non-invasive marker of enteropathy. Comparing 100 versus 100 children with two-sided alpha=0.025 (to allow for two primary comparisons, ie, HIV-SAM vs HIV-negative children with SAM, and HIV-SAM vs well-nourished HIV-positive children) provides >80% power to detect differences in mean LM ratio during hospitalisation of at least 0.16 (assuming SD 0.36), a difference which would be clinically relevant given the LM ratios previously reported for well-nourished children (0.42), malnourished children (1.3) and children with persistent diarrhoea (2.85) in the Gambia.^60^ It also provides >80% power to detect differences of at least 0.1 in the mean change in LM ratio from enrolment (assuming SD for change=0.23 and 7% missing samples). For inflammatory markers, comparing 100 versus 100 children with two-sided alpha=0.025 provides >80% power to detect differences in mean log_10_ concentrations of at least 0.44 times their SD, or 2.75-fold differences between groups. Inclusion of well-nourished controls provides an indication of normal ranges in young African children. HIV-positive and HIV-negative SAM groups will be stratified to include approximately 50 children with and without oedematous malnutrition, if possible.

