### Enteropathy substudy

The primary comparison for the enteropathy substudy will be between HIV-positive children with SAM (group A) and HIV-negative children with SAM (group C), stratified by presence or absence of oedema. Control groups (B and D) are well-nourished children with or without HIV, to provide normative data for biomarkers and to evaluate the impact of SAM within each HIV group. Thus, biomarkers among HIV-positive children with SAM will first be compared with HIV-negative children with SAM (to evaluate the impact of HIV) and, second, with well-nourished HIV-positive children (to evaluate the impact of SAM). Biomarkers among HIV-negative children with SAM will be compared with well-nourished HIV-negative children. For each continuous outcome, simple descriptive analysis will be used to compare groups during hospitalisation using t-tests on appropriately transformed data. For any outcome with moderate (p<0.05), evidence of difference between either group a regression model will be constructed including groups A, B, C and D to directly test (using interactions) whether there is a synergistic effect of HIV-SAM versus HIV-negative SAM versus HIV alone versus neither. These models will also be used to explore whether there is any evidence for heterogeneity in effects between oedematous and non-oedematous SAM. Associations between enrolment factors (eg, intestinal permeability and microbial translocation) will be explored using pairwise Spearman correlations and principal components analysis. Mean changes at the follow-up time points in each group will be estimated, and groups compared (as above) using generalised estimating equations. For outcomes that differ across SAM groups over time, multilevel models will be used to explore possible predictors from the other factors measured. Time to nutritional recovery will be compared using Kaplan-Meier and log-rank tests, and Cox models to adjust for baseline differences between groups.

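### Controls are matched to enteropathy cases by age band, but the case-control t-tests and the regression they open name no age-band term, so standard errors are probably somewhat too wide

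*Protocol article*

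**What the plan says.** Under Eligibility for enteropathy substudy, the children with SAM "are stratified into age bands (6–11 months, 12–23 months and 24–59 months) to enable age-matching of well-nourished controls". Under Well-nourished controls, the controls are "matched to enteropathy substudy children within age bands", and the source population is described thus: "Controls are children drawn from the same hospitals and communities as cases with SAM (including well-nourished sibling controls"). Study design adds that controls are "matched to children in the enteropathy substudy by age and HIV status". The strengths and limitations list gives the reason for using siblings: they are among the children from outside hospital who are added to lessen the selection bias of a hospital-only control series.

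Under Analysis, Enteropathy substudy, the first step for each continuous outcome is: "simple descriptive analysis will be used to compare groups during hospitalisation using t-tests on appropriately transformed data". The comparisons include group A with group B and group C with group D, to show the impact of SAM within each HIV group. An outcome with p<0.05 goes on to a regression on groups A to D with interactions. Neither step names age band or family.

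The sample size section treats the groups as independent. Its setting is "Comparing 100 versus 100 children with two-sided alpha=0.025", and the claim made for the LM ratio is that this design "provides >80% power to detect differences in mean LM ratio during hospitalisation of at least 0.16 (assuming SD 0.36"). It splits alpha over two primary comparisons, A v C and A v B.

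**The concern.** Matching on age band makes the age distribution alike in the two groups being compared. The part of the outcome variance that lies between age bands then no longer contributes to the error of the group difference. A two-sample t-test does not know this: it puts the whole within-group variance, including the between-band part, into its standard error. If the biomarker varies with age, the interval is wider than it need be and the test rejects less often than its nominal level.

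A v B is one of the two comparisons for which alpha was split, and the t-test result is also the gate to the interaction model. A conservative gate can keep a marker out of the model meant to examine whether HIV and SAM act together.

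The sibling controls raise a second, separate question. A t-test assumes that all children are independent, and children of one household may not be.

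**Working it through.** **Inputs from the article (Sample sizes, Enteropathy substudy).** 100 v 100 children, two-sided alpha 0.025, difference in mean LM ratio 0.16, SD 0.36.

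**Inputs not in the article (assumed).** R2, the share of within-group outcome variance explained by age band: 0.05, 0.10, 0.20. For siblings, a share f of 0.2 and a within-family correlation rho of 0.3, for illustration only.

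**Step 1: the stated power.**
SE = 0.36 × sqrt(2/100) = 0.0509. Then 0.16/0.0509 = 3.143. The critical value is 2.241. Power = Phi(3.143 − 2.241) = 81.6% (81.1% with the exact noncentral t). The stated figure above 80% is reproduced.

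**Step 2: age band.** With bands balanced between groups, the true SE of the difference is 0.0509 × sqrt(1 − R2), while the t-test still uses about 0.0509.
- Excess of the t-test SE: 1/sqrt(1 − R2) − 1.
- Real size of the t-test: 2 × [1 − Phi(2.241/sqrt(1 − R2))].
- Power of the t-test: Phi[(0.16 − 2.241 × 0.0509)/true SE].
- Power with age band in the model: Phi(0.16/true SE − 2.241).

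| Assumed R2 | True SE | t-test SE too large by | Real size (nominal 0.025) | Power, t-test | Power, adjusted |
|---|---|---|---|---|---|
| 0.05 | 0.0496 | 2.6% | 0.0215 | 82.2% | 83.7% |
| 0.10 | 0.0483 | 5.4% | 0.0181 | 82.9% | 85.8% |
| 0.20 | 0.0455 | 11.8% | 0.0122 | 84.3% | 89.8% |

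The gain is about 1.5, 3 and 5.5 percentage points.

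**Step 3: the p<0.05 gate.** The same formulas with critical value 1.960 give 88.8% v 89.7% at R2 0.05, 89.4% v 91.2% at R2 0.10, and 90.7% v 94.0% at R2 0.20. The gain is about 1 to 3 points.

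**Step 4: siblings, both directions.**
- Case and sibling on opposite sides of one contrast: variance factor 1 − f × rho = 1 − 0.06 = 0.94. The true SE is 0.970 of the t-test SE, and the real size is 0.0208: too wide.
- Siblings inside one group (20% of controls): variance factor 1 + f × rho/2 = 1.03. The true SE is 1.015 of the t-test SE, and the real size is 0.0272: too narrow.

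The article does not say which arrangement applies, or how many siblings there are.

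**The case against.** The best defence is that a journal article condenses a fuller plan, that it calls the t-tests descriptive, and that all analyses are declared exploratory. Regression models follow, and nothing says they will omit age. The fault, if any, lies on the conservative side. Much of this limits the weight of the point but does not remove it. The article names the test and makes its p-value the gate to the regression, so this is a stated method with a better alternative rather than a missing detail. Elsewhere the article does name adjustment: age, sex, oedema and baseline WHZ in the immunology infection models.

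It is also fair that the LM contrast itself is unlikely to be lost. The article cites ratios of 0.42 in well-nourished and 1.3 in malnourished children, a gap of 0.88, or about 17 standard errors (0.88/0.0509). The benefit is for markers with differences nearer the minimum that the sample was sized for.

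A reader might infer that the siblings add to the excess width and that the two features together cost substantial power. The article does not support that. It calls them siblings of children with SAM, not of enteropathy cases, so the affected sibling may be outside the substudy. A sibling whose HIV status differs from the case's falls outside that case's contrast. Siblings within one group act the other way. Siblings are included to reduce selection bias, and no paired design is described.

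**Conclusion.** The point holds in a limited form. The t-tests for A v B and C v D leave out a matching factor that the design records, and the regression they open names no term for it either. If age band is related to the marker, the standard error is somewhat too wide: about 3-12% for R2 of 0.05-0.20. That range is an assumption. With no age effect there is no loss.

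The article does not support saying that the study is underpowered, since the stated power above 80% is met by the plain t-test. Nor does it support saying that every interval is wrong: A v C involves no controls, and controls are not followed longitudinally. For siblings, the direction of the error is unknown. This is a worthwhile improvement, not a defect that threatens the conclusions.

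**What to change.** Under Analysis, Enteropathy substudy, replace the A v B and C v D t-tests with a linear model on the transformed marker, with group and the three age bands as fixed effects. Use standard errors clustered on household where sibling links exist; these serve whichever way the family correlation acts. A paired t-test would not fit, because matching is by band and not by individual pair. Carry the age-band terms and the clustering into the four-group interaction model, and base its p<0.05 gate on the adjusted comparison.

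The cost is a change of wording. Age band is already recorded for matching. A household identifier must be kept for sibling controls, and the number of siblings and the group each falls in should be reported. No further recruitment or samples are needed.

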While anthropometry is used to assess nutritional recovery after discharge from hospital, the pattern and quality of growth recovery following SAM is poorly understood. The observation that children treated for SAM have a deficit in lean tissue despite regaining weight suggests that assessing body composition in addition to anthropometry may help to identify children who have not completely recovered and are at potential risk of long-term metabolic diseases.^12^ Children with HIV-SAM appear to have potential for catch-up growth in weight-for-age and/or weight-for-height, which have been shown to normalise with treatment even prior to widespread availability of Antiretroviral Therapy (ART)^16^; by contrast, height-for-age shows less potential for catch-up growth.^17^ However, the body composition of children with HIV-SAM compared with HIV-negative children with SAM has not been described. Whether children recover fat mass at the expense of lean mass is unknown, but differences in tissue accretion patterns may have implications for survival and long-term metabolic health.^18 19^ There is also a need to consider the effect of SAM on the size of body parts which grow at different rates: relatively shorter legs, for example, are associated with epidemiological risk of overweight, coronary artery disease, liver dysfunction and diabetes.^20 21^

Taken together, there is clearly an elevated risk of mortality among HIV-positive children with SAM compared with HIV-negative children with SAM, and an ongoing mortality risk among all children with SAM that persists after discharge from hospital. There are several gaps in our understanding of the long-term outcomes: (i) causes of death have not been clearly defined, (ii) no studies have systematically and longitudinally collected morbidity and mortality data or documented repeat hospitalisations post discharge and (iii) the long-term outcomes of HIV-positive children with SAM in the era of ART availability are unclear.

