## Recruitment

### Screening

Caregivers of all hospitalised children are sensitised about the study. All new admissions aged 0–59 months are screened for SAM, which is defined according to WHO criteria as any of WHZ <–3, MUAC <115 mm (if aged 6–59 months) and/or bilateral pitting oedema. All children with SAM are recruited from hospital, and this study therefore focuses on complicated SAM; children with uncomplicated SAM will not be enrolled.

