### Microbiota substudy

Normal assembly of the gut microbiota in early life is critical for many aspects of physiological, neurological and immune development.^38^ Recent evidence suggests that an immature or pathogenic microbiota plays a causative role in the pathogenesis of SAM.^25^ For example, a number of microbial taxa have been identified, including *Faecalibacterium prausnitzii*, which discriminate and predict gut microbiota maturity and child growth.^28^ Other pathogenic microorganisms, including IgA-targeted *Enterobacteriaceae*, are associated with impaired growth and may contribute to SAM.^39^ Nutritional rehabilitation with RUTF induces temporary recovery of a disturbed microbiota; however, the microbiota appears to revert back to an immature diseased state following nutritional recovery.^29^ HIV infection is also associated with a disturbed gut microbiota,^40^ which may further compound enteropathy phenotypes. Furthermore, there is some evidence that differences exist in malnutrition enteropathy between oedematous and non-oedematous SAM^41^; however, few studies have investigated differences in the gut microbiota between the two forms of the disease.

We hypothesise that (i) a unique gut microbial signature exists in HIV-SAM, compared with HIV-negative children with SAM, that is independently associated with morbidity, mortality, nutritional recovery and degree of enteropathy during hospitalisation; (ii) a unique gut microbial signature exists in oedematous compared with non-oedematous SAM; (iii) specific microorganisms or gut microbial diversity indices are independently associated with morbidity, mortality, nutritional recovery and degree of enteropathy during hospitalisation; and (iv) the gut microbiota is partially restored to a healthy state with nutritional rehabilitation but reverts to a dysbiotic state during follow-up, which predicts morbidity, mortality and relapse of SAM.

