## Time frame and study status

“Enrolment into the SAM cohorts began in July 2016 and ended in March 2018. Enrolment of well-nourished controls is expected to end in March 2019. All participants with SAM will be followed for 48 weeks, with an expected study completion date of March 2019.”

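### Well-nourished controls are defined nutritionally by current WHZ >–1 alone, so children who are SAM by the protocol's own MUAC criterion, and children recovered from SAM, can enter the reference group

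*Protocol article*

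**What the plan says.** The Well-nourished controls section of the protocol article requires controls to be aged 6–59 months, matched by age band, and "well-nourished (WHZ >–1) and clinically well (no acute illness or current infections) with known HIV status". It then lists exclusions: "Children with underlying chronic gastrointestinal disease or a known malignancy are ineligible". The column heading of Table 1 repeats the single nutritional limit: "Well-nourished controls WHZ>–1". Neither place mentions MUAC, oedema or an earlier episode of malnutrition. Controls come from the same hospitals and communities as the cases and may be siblings.

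The Screening section defines SAM as "any of WHZ <–3, MUAC <115 mm (if aged 6–59 months) and/or bilateral pitting oedema". Any one of the three is sufficient.

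On recovery, the Long-term outcomes section says: "Children with HIV-SAM appear to have potential for catch-up growth in weight-for-age and/or weight-for-height". It adds that treated children keep a lean-tissue deficit after regaining weight, and cites a seven-year follow-up in which former SAM patients still did worse than siblings and community controls. The Microbiota substudy section says that "the microbiota appears to revert back to an immature diseased state following nutritional recovery".

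On use, the Enteropathy analysis section states: "Control groups (B and D) are well-nourished children with or without HIV, to provide normative data for biomarkers". It also uses them to estimate the effect of SAM within each HIV group. The Well-nourished controls section makes them the comparison group for all laboratory substudies.

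**The concern.** The case definition and the control definition do not exclude each other. Cases qualify on any of three signs, whereas controls are cleared on one. The sign used to clear controls, WHZ, is also the one that the article says can normalise while other abnormalities remain.

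A reference group that includes current or former SAM children would understate the difference between SAM and health. It would also make incomplete recovery look more normal, which matters because several hypotheses concern partial restoration or relapse toward an abnormal state. The contrasts exposed are HIV-positive SAM v HIV-positive controls (A v B), HIV-negative SAM v HIV-negative controls (C v D), the HIV-by-SAM interaction built from all four groups, and the normative ranges.

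**Working it through.** **Do the definitions overlap?** Take a child aged 30 months, WHZ –0.5, MUAC 113 mm, no oedema, no acute illness, HIV status known.

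| Rule | Result |
|---|---|
| Screening: any of WHZ <–3, MUAC <115 mm, oedema | SAM, on MUAC |
| Controls: age 6–59 months | met |
| Controls: WHZ >–1 | met |
| Controls: clinically well, HIV status known | met |
| Controls: no chronic gastrointestinal disease or malignancy | met |

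The child is SAM and eligible as a well-nourished control. If MUAC is instead normal but the child was treated for SAM a year earlier, every control criterion is still met.

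**The plan's own power figure.** Inputs from the Enteropathy sample-size section: 100 v 100, difference in lactulose-mannitol (LM) ratio 0.16, SD 0.36, two-sided alpha 0.025.

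- Power = Φ[(0.16/0.36) × √(100/2) – 2.241] = Φ(3.143 – 2.241) = Φ(0.901) = 81.6%.

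The stated figure of more than 80% reproduces. It presumes a clean reference group.

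**What dilution would do (illustration only).** Let a fraction f of controls keep a share r of the SAM-versus-healthy gap Δ. The observed gap is Δ(1 – f·r), with the SD held at 0.36. The documents give neither f nor r.

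| Assumed f, r | Gap if Δ = 0.16 | Power |
|---|---|---|
| 0 | 0.160 | 81.6% |
| 5%, 0.5 | 0.156 | 79.5% |
| 5%, 1 | 0.152 | 77.2% |
| 20%, 0.5 | 0.144 | 72.1% |
| 20%, 1 | 0.128 | 60.7% |

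The value 0.16 is the smallest difference the design was sized to detect. It is not the expected SAM-versus-control gap. The same section quotes LM ratios of 1.3 in malnourished and 0.42 in well-nourished children: Δ = 1.3 – 0.42 = 0.88, or 0.88/0.36 = 2.4 SD. Even if half the controls kept 70% of that gap (f·r = 0.35), the observed gap would be 0.88 × 0.65 = 0.57, or 1.6 SD, and power would remain essentially 100%. At a gap of that size the consequence is a biased estimate, with no material loss of power.

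**Interaction.** With the same SAM effect Δ in both HIV groups, the bias in (A – B) – (C – D) is –(f_B – f_D)·r·Δ. It is zero if both control groups are equally affected. With f_B = 20%, f_D = 5% and r = 1 (all assumed), it is –0.15 × 0.16 = –0.024, or –0.15 × 0.88 = –0.132.

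**The case against.** **The full protocol may hold further exclusions.** The article points to an online protocol, and the flow chart is not shown. This is possible. However, the article states the control criteria and exclusions explicitly, and gives the nutritional limit twice, so it is a rule stated too loosely and not a detail left out. If stricter criteria exist, the article should carry them.

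**Other wording narrows the overlap.** The requirement to be clinically well would probably remove children with oedema. A well child with low MUAC would appear to have uncomplicated SAM, and so would not be a study case either. Both points are fair. Neither makes that child well nourished by the protocol's definition, and neither touches past SAM.

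**The persistence evidence is indirect.** A lean-tissue deficit is not a laboratory biomarker, and metabolic reversion is a hypothesis under test. This stands, and it is why r cannot be fixed.

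**The main comparisons do not use controls.** The analysis sections name A v C as primary for enteropathy, and oedematous v non-oedematous HIV-negative SAM for microbiota and metabolomics. These are unaffected, and all analyses are declared exploratory. The sample-size section does, however, count A v B among the two primary comparisons for which alpha was divided.

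**Excluding past SAM changes the question.** Cases need not be first episodes. Removing past SAM from controls only would apply a history rule to one side and could leave group B as a selected, healthier subset. This stands, and it shapes the fix.

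**A stronger reading is tempting.** A reader might infer heavy contamination concentrated in group B, because the article says many HIV-infected children present late with malnutrition and that malnutrition reaches 40% of HIV-positive children in some settings. Those statements do not give the share of currently well children with WHZ above –1 who had SAM, so they support neither a rate nor a B-versus-D difference.

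**Conclusion.** The concern holds as a defect in the eligibility rule. By the protocol's own wording, a clinically well child with MUAC below 115 mm can be both SAM and a well-nourished control, and a recovered SAM child can be a control. The likely direction is toward the null for A v B and C v D, with a blurred normative range. This assumes that such children's biomarkers lie between healthy and SAM values. The size cannot be derived from the document, nor can it be said whether group B is more affected than group D.

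A reader might take the power table as showing that the control contrasts are underpowered. The document does not support that: the losses arise at the minimum detectable 0.16 under assumed f and r, and largely vanish at the quoted gap of 0.88. Comparisons confined to SAM children are not affected.

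**What to change.** The timetable still allowed a change when the article was written: "Enrolment of well-nourished controls is expected to end in March 2019".

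1. Amend the Well-nourished controls section and Table 1 so that a control meets none of the protocol's own SAM criteria, covering MUAC and oedema as well as WHZ.
2. Record past treatment or admission for acute malnutrition in every control, by caregiver report or handheld record. For controls already enrolled, obtain this and MUAC where possible.
3. Keep the currently well-nourished group as the main reference. Whether the reference should instead be never-malnourished children is a choice of estimand and should be stated as such.
4. Add a sensitivity analysis of A v B, C v D, the HIV-by-SAM interaction and the normative ranges that leaves out controls with past SAM or MUAC below 115 mm. Show it beside the all-controls result.

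The cost is one history question, one MUAC check, a minor amendment and a re-run of the control contrasts. The downside is a somewhat smaller group B in the sensitivity analysis.
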